#### Retrospective cohort

We will initially perform a retrospective study of stored maternal serum microbiology samples and Down Syndrome screening samples taken in the first trimester from MC twin pregnancies as part of routine booking at Birmingham Women’s NHS Foundation Trust. These samples are routinely stored for 2 years in the microbiology and clinical chemistry department, and equate to approximately 170 samples. We will measure maternal angiogenic factors and placental growth factors in these samples, collect first trimester ultrasound measurements (CRL and NT) and patient characteristics and pregnancy outcome data. As Down Syndrome screening samples are received from 31 sites in the UK, we will ask clinicians at these sites to assist in data collection using a pre-designed proforma. Where clinicians feel unable to help with data collection, we will visit the sites and collect the outcomes ourselves. The primary outcome will be whether participants developed a complication in pregnancy (TTTS, TAPS, sIUGR, single or double intrauterine demise) and the severity of these complications. Secondary outcomes will include delivery (gestation at delivery, mode of delivery, birth weight, condition of twins at delivery) and neonatal outcomes (admission to neonatal unit, diagnosis of comorbidity, particularly neurological). The maternal angiogenic factors and placental growth factors measured will be decided based on our preliminary work (see above) and a systematic review and individual patient data (IPD) meta-analysis (see PROSPERO CRD42015024975 for full protocol). As this is a retrospective study and the results of our study will not affect patient care, patients whose blood samples we are using in this retrospective study will not be consented or informed of the results. However, all women under the care of Birmingham Women’s NHS Foundation Trust are aware that the hospital is research active, and that their blood samples may be used in this way, and are given the option of opting out if they so wish. Samples from patients who have indicated that they do not want their samples to be used for research will be excluded from this study. This retrospective study will inform the subsequent prospective study.

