#### Prospective cohort

The prospective study will run over 2 years (August 2015–August 2017) and there will be 2 cohorts: a “screening” MC twin cohort (Cohort S), and a cohort who have developed complications (Cohort C) (see Fig. 1). In both cohorts, informed written consent will be obtained. The “screening” cohort (Cohort S) will be approached in the ‘multiples’ antenatal clinic where all twin pregnancies are managed at Birmingham Women’s NHS Foundation Trust. We will ask participants with confirmed MC twin pregnancies to consent to 2 extra bottles of blood being taken during their routine Down Syndrome blood test or booking blood tests, and for permission to record their first trimester ultrasound measurements, and access the above outcome data as specified in the retrospective study. We will then repeat the blood sampling at 16 weeks and 20 weeks gestation when they attend for routine ultrasound scans. If the participant does not develop any complications, this will be the end of her involvement in the study and we will just collect the outcome data. However, if she develops a complication (e.g. TTTS, TAPS, sIUGR, single intrauterine demise) she will be invited and consented to enter the second prospective “complicated” cohort.

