### Data management and data analyses

At recruitment, each participant will receive a unique study identifier to allow linkage of data. Data will be collected using a purposely designed proforma (as per the retrospective cohort) and manually input onto a secure electronic database. Hard-copies of data will be kept in a locked filing cabinet, in a swipe-card access department at Birmingham Women’s NHS Foundation Trust. We will ensure that we remain compliant with the Trust’s Information Governance policies at all times.

Descriptive data will be reported. First trimester ultrasound measurements (NT and CRL) and serial serum biomarkers will be compared between participants in cohort S who go on to develop complications, and participants in cohort S who do not develop complications. The serum biomarker results from the 16 and 20 week blood samples from participants in cohort S will also act as the control group for cohort C participants. Additionally serum and amniotic fluid biomarkers will be compared longitudinally (i.e. pre- and post-FLA) for each participant in cohort C, to evaluate the potential effect of FLA on the biomarkers. The appropriate statistical tests will be used. Chi-squared will be used for categorical variables, and student’s t-test (paired and unpaired where appropriate) for continuous variables. Logistic regression models will be created to assess the association between variables and outcomes and presented as odds ratios (OR) with a 95% confidence interval (CI). Different cut-offs will be used for TTTS (Quintero staging) and sIUGR (EFW <10^th^ centile, <5^th^ centile).

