## Discussion

This study aims to increase knowledge surrounding the pathology of complications in MC twins, which in turn is hoped to aid future diagnosis and management. To our knowledge, this is the first study to look at these serum and amniotic fluid biomarkers in such a large cohort of MC twin pregnancies.

Although we are one of the largest Fetal Medicine Centres in the UK, the number of participants eligible for inclusion is insufficient to power the development of a prediction model, and may cause false negative results. The results of this study may inform a larger, multi-centre study to be conducted over several years so as to create a prediction model to triage MC twin pregnancies as high-risk or low-risk for complications, and thus requiring more or less surveillance antenatally.

There will be some women who will have booked at Birmingham Women’s NHS Foundation Trust and will be recruited to both the first-trimester screening cohort and the “complicated” cohort. Parents are routinely informed of the potential complications of MC pregnancy at booking, and by seeing these women in the first-trimester, this will give us the opportunity to inform them of the second part of the prospective study and they will have at least 4 weeks to consider participation should a complication develop. However, as a tertiary Fetal Medicine Centre we receive a lot of referrals from around the UK for second opinions and to perform treatment for MC twin complications, e.g. FLA. These referred patients will also be eligible for inclusion in the “complicated” cohort, although we will not have first-trimester blood samples for them. Unfortunately, due to the rapid progression of complications, these parents may have a limited time to consider participation. However, this is still in-keeping with ethical approval.

Although we will be unable to gain consent for participants in the retrospective study, we intend to publish our results on the TAMBA website to which the public have access. We also hope to present them at international conferences and publish in leading medical journals.

We expect to lose some participants to follow-up, and to be unable to collect outcome data for some patients who may have moved areas, or have had their baby(ies) transferred out to different neonatal units.

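### Marker levels in cohort C and cohort S are to be compared by an unadjusted t-test, although most cohort C women probably come from outside the controls' hospital, so population differences can be mistaken for disease effects

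*Protocol article*

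**What the plan says.** Under Data management and data analyses, the article names the controls for cohort C (the quote stops just before that letter): "serum biomarker results from the 16 and 20 week blood samples from participants in cohort S will also act as the control group for cohort". For the tests, it assigns chi-squared to categorical variables and Student's "t-test (paired and unpaired where appropriate) for continuous variables". It then adds: "Logistic regression models will be created to assess the association between variables and outcomes", reported as odds ratios with 95% intervals and without named covariates.

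The two groups are recruited differently:

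- **Cohort S** (Prospective cohort) is approached in the "antenatal clinic where all twin pregnancies are managed at Birmingham Women"'s.
- **Cohort C** (Discussion) is open to outside referrals: "we receive a lot of referrals from around the UK for second opinions and to perform treatment for MC twin complications". The same section says that some Birmingham-booked women "will be recruited to both the first-trimester screening cohort and the" complicated cohort.

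On covariates, the Retrospective cohort section plans to "collect first trimester ultrasound measurements (CRL and NT) and patient characteristics and pregnancy outcome data". The prospective proforma is described only as being like the retrospective one. No list of characteristics is given.

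**The concern.** Comparing C with S is an observational case-control contrast, and an unpaired t-test takes no covariates. It reads the whole difference in mean marker level as the difference between complicated and uncomplicated pregnancy. That is sound only if the groups are otherwise comparable, and the recruitment routes give no reason to expect this. The controls are one hospital's booked women. The recruitment estimate for cohort S also counts only the 70% who accept Down syndrome screening, a step that cohort C does not pass through.

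Gestation adds to the problem. Controls are sampled at 16 and 20 weeks, while the Background places TTTS usually between 15 and 26 weeks. The group's previous work, as described in the Background, matched for gestational age; nothing equivalent is stated here.

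At stake is whether a marker difference between C and S can be attributed to the complication. These results are meant to inform a larger multi-centre study, so a spurious marker could be carried forward, or a real one masked.

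**Working it through.** **1. Reproduce the recruitment figures (Expected number of participants).**

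- Cohort S: 7,900 × 0.02 = 158 multiple pregnancies a year; × 0.30 = 47.4 MC; × 0.70 = 33.2; − 5 = 28.2; × 2 years = 56.4. The article says 56.
- Cohort C: (80 to 120) × 0.50 = 40 to 60, as stated.

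**2. How much of cohort C is likely to be referred?** Inputs: 47.4 MC pregnancies a year at Birmingham, TTTS in 10-15% (Background), and 80-120 women treated over 2 years.

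- Birmingham-booked TTTS over 2 years: 94.8 × 0.10 = 9.5 to 94.8 × 0.15 = 14.2.
- Share of those treated: 9.5/120 = 8% to 14.2/80 = 18%. So about 82-92% booked elsewhere.
- If every Birmingham-booked case joined cohort C, their share would be 9.5/60 = 16% to 14.2/40 = 36%. Referred women would still be 64-84%.
- Women in both cohorts: 56 × 0.10 = 5.6 to 56 × 0.15 = 8.4 TTTS cases from cohort S, which is 5.6/60 = 9% to 8.4/40 = 21% of cohort C.

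**3. What an imbalance would do to the t-test.** The article gives no data on this, so all inputs here are assumptions: two-sided 5%, 50 cases against 56 controls treated as independent, and no disease effect. Maternal characteristics explain a share R² of marker variance and differ by s SD between groups.

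- Induced marker shift: d = √R² × s.
- Standard error in SD units: √(1/50 + 1/56) = 0.195.
- Rejection probability: 1 − Φ(1.96 − d/0.195) + Φ(−1.96 − d/0.195).

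| R² | s (SD) | d (SD) | Unadjusted, formula | Unadjusted, simulated (two sets of 8,000 runs) |
|---|---|---|---|---|
| 0.10 | 0.2 | 0.063 | 6.2% | 5.8%, 6.2% |
| 0.15 | 0.3 | 0.116 | 9.2% | 9.2%, 8.9% |
| 0.20 | 0.5 | 0.224 | 21% | 20.1%, 20.3% |

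A linear model adjusted for the characteristic rejected in 4.7-5.2% of the simulated runs. That holds because the simulated characteristic was the only imbalance.

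**4. Power under the same assumptions, true effect 0.5 SD, R² = 0.15.**

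- No imbalance, unadjusted: 0.5/0.195 = 2.57, power 73% (simulated 72-73%).
- No imbalance, adjusted: residual SD √0.85 = 0.922, so 0.5/(0.195 × 0.922) = 2.79, power 80% (simulated 78-79%).
- Imbalance of 0.3 SD acting against the effect: unadjusted (0.5 − 0.116)/0.195 = 1.97, power 50% (simulated 49-50%); adjusted 77% (simulated).

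**The case against.** The strongest reply is that the plan already contains a regression. A logistic model with complication as outcome, and the marker plus patient characteristics as variables, could adjust the same contrast. A condensed article may leave the covariate list to the full protocol or analysis plan. This stands in part. A reader might infer that the whole analysis ignores patient characteristics; the document supports that only for the t-tests. But the article does not say that the logistic model covers C versus S or includes those characteristics, and an odds ratio does not replace the stated comparison of marker levels.

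Other points also stand and limit the claim:

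- A reader might infer that population differences will pass as disease effects. The article gives no data on how the populations differ or on which characteristics affect these markers. Only *can* is supported.
- A reader might take cohort C as wholly drawn from distant centres. It is mixed. Some women are Birmingham-booked, and women who booked elsewhere may include some from nearby hospitals; the article gives no split.
- A reader might assume that particular covariates are already on the form. None is named, and their collection in the prospective cohorts is inferred from the likeness of the proformas. That the change needs no new data is therefore unconfirmed.
- The referral argument does not reach complicated versus uncomplicated women within cohort S, who come from the same clinic, or the within-woman comparison before and after laser treatment.
- The article already describes its numbers as too few for a prediction model and warns of false negatives. That caveat covers low power, not bias.

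**Conclusion.** The concern holds for one contrast, C versus S marker levels. The article fixes the control group and names a test that cannot take covariates. By its own figures most cases probably come from a different booking population (82-92% of treated women; at least 64% of cohort C even if every Birmingham-booked case joined). It states neither matching nor adjustment for that comparison.

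The amount of bias cannot be established from the document. The 6-20% false-positive range, with about 9% at R² 0.15 and a 0.3 SD shift, illustrates what modest imbalances would do. The upper end needs both assumptions at their maximum. This is an improvement that should be made because it is cheap and the route for confounding is built into the recruitment; it is not proof that the results will be wrong.

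**What to change.** State that the C versus S comparison will use a linear model on the suitably transformed marker, containing:

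- group;
- gestation at sampling;
- a short prespecified list of maternal characteristics recorded at booking, before disease, so that the complication cannot have altered them. The sponsor should first confirm that these are on the proforma and obtainable for women referred from other hospitals.

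Count each woman once, or use a model that allows for women who are in both cohorts and for controls who contribute both a 16- and a 20-week sample. Report the unadjusted difference alongside. Because the marker is the response, all of the roughly 100 women (40-60 cases and 56 controls) contribute to estimating the covariate effects.

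Within cohort S the same model is optional and offers precision only. The paired pre/post-laser analysis needs no change on this account.

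Cost: a change of analysis wording if the characteristics are collected, and added proforma items if they are not. The analysis loses a few degrees of freedom, and some women will have a missing covariate. Adjustment removes only imbalance in what is measured, so the report should still describe the two recruitment routes and the number of cohort C women booked at Birmingham.

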## Discussion

This study aims to increase knowledge surrounding the pathology of complications in MC twins, which in turn is hoped to aid future diagnosis and management. To our knowledge, this is the first study to look at these serum and amniotic fluid biomarkers in such a large cohort of MC twin pregnancies.

Although we are one of the largest Fetal Medicine Centres in the UK, the number of participants eligible for inclusion is insufficient to power the development of a prediction model, and may cause false negative results. The results of this study may inform a larger, multi-centre study to be conducted over several years so as to create a prediction model to triage MC twin pregnancies as high-risk or low-risk for complications, and thus requiring more or less surveillance antenatally.

There will be some women who will have booked at Birmingham Women’s NHS Foundation Trust and will be recruited to both the first-trimester screening cohort and the “complicated” cohort. Parents are routinely informed of the potential complications of MC pregnancy at booking, and by seeing these women in the first-trimester, this will give us the opportunity to inform them of the second part of the prospective study and they will have at least 4 weeks to consider participation should a complication develop. However, as a tertiary Fetal Medicine Centre we receive a lot of referrals from around the UK for second opinions and to perform treatment for MC twin complications, e.g. FLA. These referred patients will also be eligible for inclusion in the “complicated” cohort, although we will not have first-trimester blood samples for them. Unfortunately, due to the rapid progression of complications, these parents may have a limited time to consider participation. However, this is still in-keeping with ethical approval.

Although we will be unable to gain consent for participants in the retrospective study, we intend to publish our results on the TAMBA website to which the public have access. We also hope to present them at international conferences and publish in leading medical journals.

We expect to lose some participants to follow-up, and to be unable to collect outcome data for some patients who may have moved areas, or have had their baby(ies) transferred out to different neonatal units.

## Conclusions

This study hopes to increase knowledge of the pathological processes involved in the continuum of MC twin complications, and allow us to predict which MC twins will develop complications so that we are better able to target surveillance and therapy, and ultimately improve outcomes for these families.

## Abbreviations

Ang-2: Plasma angiopoietin
CI: Confidence interval
Cohort C: “Complicated” cohort
Cohort S: “Screening” cohort
CRL: Crown rump length
EFW: Estimated fetal weight
FLA: Fetoscopic laser ablation
IPD: Individual patient data
MC: Monochorionic
NT: Nuchal translucency
OR: Odds ratio
PAPPA: Pregnancy associated plasma protein A
PlGF: Placental growth factor
sFLT-1: Soluble fms-like tyrosine kinase-1
sIUGR: Selective intrauterine growth restriction
sVEGFR-1: Soluble vascular endothelial growth factor receptor-1
TAPS: Twin anaemia polycythaemia sequence
TTTS: Twin-twin transfusion syndrome
VEGF-C: Plasma vascular endothelial growth factor
αFP: Alpha feto-protein
β-hCG: Beta human chorionic gonadotrophin
